## Abstract

**Background:**

Studies have shown that the prevalence of overweight, obesity and diabetes are higher in the largely Hispanic, immigrant farmworker population in California. Though to date, few interventional studies have focused on these issues in this at-risk population. The objective of this paper is to describe the study design of a cluster randomized controlled trial aimed at evaluating the effectiveness of an obesity and diabetes work place intervention in an immigrant farm worker population.

**Methods:**

PASOS is an obesity and diabetes intervention program that will be implemented on ranches where immigrant farmworkers spend a considerable amount of time each day. This cluster randomized controlled study will enroll approximately 600 farmworkers. Using a uniform distribution for random number generation, ranches are randomized using a 1:1 ratio as either control or intervention. Baseline data will be taken from eligible participants and analyzed against data collected at the post-intervention, 6-month, 1-year, and 1.5-year follow-ups. The enrollment period is 1.5 years.

**Discussion:**

Few studies have been conducted that aim to evaluate the effectiveness of a worksite intervention for obesity and diabetes prevention in a largely Hispanic, farmworker population. This study has been tailored to this population in order to enhance the feasibility of implementation and retention. If successful in reducing obesity and increasing healthy lifestyle choices to reduce diabetes, this study design can be implemented on a larger scale.

**Trial registration:**

NCT02480244. Registered 24 June 2015.

**Electronic supplementary material:**

The online version of this article (10.1186/s12889-018-5560-0) contains supplementary material, which is available to authorized users.

## Background

Diabetes and obesity are rapidly increasing health problems in the United States (U.S.) and worldwide [1]. It is estimated that in the U.S., 29.1 million people have diabetes, almost 28% are undiagnosed [2, 3]. National estimates suggest that 12.1% of Hispanics have diagnosed diabetes (4.7% undiagnosed) and that the risk of diagnosed diabetes is 66% higher among Hispanics compared to non-Hispanic white adults [4, 5]. (Note: in this paper, usage of the terms Hispanic or Latino is based on terminology used in the referenced publication. The term Latino will be used to reference our study population.). Similarly, national data document alarming increases over the past several decades in overweight, obesity and extreme obesity [6]. Among Hispanic or Latinos aged 20 and over, the combined prevalence of overweight and obesity is 78.4%, markedly higher compared to the general population [7]. Additionally, Latino populations in the U.S. not only have high rates of diabetes and obesity, but also face higher prevalence of metabolic syndrome and cardiovascular complications from these chronic diseases. Cardiovascular diseases are the leading cause of death of Latinos in the U.S. [8]. Among this population, type 2 diabetes develops at younger ages, with higher rates of complications and mortality, the higher prevalence is further compounded by lifestyle, socioeconomic, and cultural factors [9].

There are over 55 million Latinos living in the U.S., comprising 17% of the total population. The nation’s Latino population, which was 35.3 million in 2000, grew 46.3% over the decade [9, 10]. It is projected that by 2060, Hispanics will represent almost 30% of the total U.S. population [10]. It is estimated that 27.8% of the total Hispanic population reside in California [11]. Nationally over 2.6 million people are employed in agricultural labor over half of which are farmworkers [12]. It is estimated that there are over 829,000 people employed in agriculture in California [13]. While Hispanics account for only 16% of total employment, they make up approximately 96% of hired crop workers in California [14, 15].

Studies have found that the prevalence of obesity is elevated among the Hispanic population in California [16–18]. The farmworker paradox is contrary to the expected finding that farmworkers, who put in long days of physical labor, would have lower rates of overweight and obesity, but it illustrates the breadth and seriousness of this problem in low-income immigrant Latino populations. California farmworkers and other immigrant Latino workers in low-wage industries face disadvantages in prevention and management of these problems [19]. Compounding the problem are low family incomes, limited access and utilization of health services, and limited knowledge of and access to healthy foods [20–22].

Latino farmworkers make up a large and important segment of our workforce who are at high risk of obesity and diabetes. There are currently no known interventions targeting this population at the agricultural worksite, a promising venue for lifestyle interventions among a population that spends considerable time working. The goal of the worksite intervention is to target individuals at-risk for obesity and diabetes and promote changes in behavioral and lifestyle risk factors.

### Preliminary data from pilot study

In 2010, University of California, Davis (UCD) collaborated with Reiter Affiliated Companies (RAC), the largest fresh multi-berry producer in the world, growing Driscoll’s proprietary varieties of strawberries, raspberries, blueberries, and blackberries year round in the US, and other international locations, on a pilot study [23]. In this randomized controlled study, 254 participants were allocated to either the control or intervention group in a 1:2 ratio for control:intervention. Farmworkers employed by RAC participated in a 10-week diabetes and obesity prevention program developed by UC Davis and delivered in Spanish by *promotores*. The majority of participants were born in Mexico and identified Spanish as their native language. Primary outcomes included change in weight, body mass index (BMI), waist circumference, and fasting blood glucose concentration. Secondary outcomes assessed changes in diet and physical activity. The pilot found small but significant reductions in weight, BMI and waist circumference in participants completing the program; the decreases were statistically significant in women, but not in men. Improvement in knowledge of healthy eating such as the number of recommended servings of fruits and vegetables, how much water to drink and how much to exercise per day was also seen. Self-reported behaviors related to a healthy lifestyle also changed in the positive direction. Participants who completed the program reported increased physical activity as well as changing their eating habits, such as eating more fruit and less fast food, drinking more water and fewer sweetened drinks. Participant retention was high, with 70% overall remaining in the study from baseline to post-intervention [23]. After the successful completion of the pilot study, we aim to implement and evaluate the effectiveness of the program on a larger scale by recruiting more participants and with a longer follow-up period. The central hypotheses of this project are that a lifestyle intervention delivered at the agricultural worksite will reduce obesity and diabetes risk for employees and will prove to be cost effective for the employer.

## Methods

### Study design

A cluster randomized trial (CRT) design is being used to evaluate the effectiveness of a worksite lifestyle intervention in producing changes in factors known to increase risk of obesity and diabetes [23]. Ranches allocated to the intervention group will receive the worksite intervention program over 6–12 weeks. Ranches allocated to the control group will receive no intervention but will be given the opportunity to attend other educational sessions, topics covered will not be the same as those covered in the intervention program and may include such topics as communication and conflict resolution specifically geared towards farm workers. The study period is 5 years. Recruitment and enrollment of subjects is expected to take 2 years. Recruitment at ranches will be staggered so that as work crews have a sufficient number of interested participants and baseline assessments are completed, the educational sessions will begin on designated ranches. A subject’s participation in the study will begin with their consent and end after a 1.5-year follow-up data collection point, or at an earlier date if they choose to withdraw from the study (Fig. 1).

**Fig. 1 Fig1:**
[figure not shown]
Study design

As part of this study, process evaluation strategies will also be reviewed. Qualitative and quantitative methods will be implemented to improve and maintain participation in the program and assess participant satisfaction. Process evaluation will continue throughout the length of the study to provide ongoing data and evaluation to guide the intervention.

We will also conduct an economic evaluation on the ranches offering the program relative to the control ranches. The objective is to document the commercial viability of ongoing programs in the berry industry and perhaps more widely among other agricultural industries as well as other industries that employ largely immigrant populations. In addition, we will evaluate the cost of the intervention relative to the health benefit achieved by participants. This analysis will exclude costs of administering the evaluation of the study but will include all costs associated with the delivery of the intervention itself. This study protocol was approved by the University of California, Davis, Office of Research, Institutional Review Board Administration (#575576).

### Study population

All potential subjects are seasonal, immigrant farmworkers with low income and education levels. Workers interested in participating in the study must meet the following inclusion criteria (1) work at Reiter Brothers, Inc. (RBI), a partner or affiliate company, (2) be at least 18, (3) plan to stay in the area for the next 3 months, (4) be willing to attend weekly sessions for the length of the educational sessions, and (5) be able to speak Spanish and to read well enough in Spanish to follow basic instructions. Exclusion criteria is as follows, (1) workers without Spanish language comprehension, (2) pregnant women and those planning a pregnancy within 6 months, (3) women who are breastfeeding, unless discontinuing breastfeeding within 1 month, (4) individuals who, without health care provider approval, are: unable to undertake moderate physical exercise, taking medicine for high blood pressure or heart conditions, have bone or joint problems, lose consciousness or fall due to dizziness, or have developed chest pain within the last month, (5) individuals taking medications that affect weight, (6) individuals with therapeutic diets, (7) previous diabetes diagnosis disclosed during screening or diabetic status determined by Hemoglobin A1c (HbA1c) testing with levels ≥6.5% who will be referred to the clinic for medical attention, (8) individuals with a spouse/cohabitant already enrolled in the study, and (9) individuals who have previously participated in *Sembrando Salud* (RAC version of PASOS) within the last 4 years.

### Recruitment

*Promotores* will visit crews on the selected ranches twice to hold information sessions to inform workers about the study. Interested participants will be given a chance to provide their name and contact information for follow-up. Research assistants will follow-up with interested participants by phone to set up an appointment to be administered a screening questionnaire to determine their eligibility to participate in the study. Research assistants will schedule eligible individuals for an in-person meeting to obtain consent and to collect baseline data. Information sessions about the program will emphasize that participation is voluntary and will not affect employment. All information presented to workers will be culturally tailored and delivered in Spanish by bilingual staff.

### Randomization

Randomization will take place at the ranch level prior to recruitment of participants into the study. Two ranches matched on location, type of berry, size (whenever feasible) will be randomized with the 1:1 ratio sequentially when the two ranches are available for participation, using a uniform distribution for random number generation. At least six ranches will be randomized to intervention or control. We will recruit approximately 100 workers at each ranch. In total, the study will recruit up to 600 workers. Due to the nature of the intervention and because the intervention takes place at the ranch, the participants as well as the research assistants collecting data will not be blinded.

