9	Healthy portions
10	Choosing healthy meals 1
11	Choosing healthy meals 2
12	Review and Graduation

The intervention will be conducted by *promotores* who will receive extensive training on curriculum content; framework of the intervention; group management skills and implementation of the intervention. In addition, the *promotores,* will be taught effective presentation delivery skills to ensure that they understand the material and are able to motivate and support participants.

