#### Control

Control participants will be given the opportunity to attend educational sessions as well, although these sessions will not have the same topics as those received by the intervention participants. The control sessions will utilize RAC leadership training material for farmworkers on: empathy, communication, conflict resolution, and sharing knowledge. Sessions for control participants will also be held at the ranch during a meal break. Recruitment and follow-up for control participants will follow the same approach as those for intervention participants.

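### Ranches are allocated before workers are approached, consented and measured, and nothing says the allocation is withheld, so who volunteers may depend on arm

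*Protocol article*

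**What the plan says.** All references are to the protocol article.

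- **Order of steps.** The Randomization section says "Randomization will take place at the ranch level prior to recruitment of participants into the study". Table 3 agrees: allocation has the first column, followed by eligibility screening and then by consent and baseline.
- **First approach.** The Recruitment section says promotores "will visit crews on the selected ranches twice to hold information sessions to inform workers about the study". Interested workers then leave their contact details.
- **Screening, consent, baseline.** Research assistants arrange and administer the screening questionnaire. Then: "Research assistants will schedule eligible individuals for an in-person meeting to obtain consent and to collect baseline data".
- **Blinding.** The Randomization section says "the participants as well as the research assistants collecting data will not be blinded".
- **Entry criterion.** In the Study population section, a worker must "be willing to attend weekly sessions for the length of the educational sessions".
- **What the sessions are.** Table 1 lists BMI, diabetes, portions and healthy meals for intervention ranches. The Control section says of its own sessions that "these sessions will not have the same topics as those received by the intervention participants"; they use leadership material such as communication and conflict resolution.
- **Start of sessions.** Under Study design: "Recruitment at ranches will be staggered so that as work crews have a sufficient number of interested participants and baseline assessments are completed", the sessions begin. Sessions therefore already wait for baseline.
- **Possible safeguards.** The Control section says that controls are recruited in the same way as intervention participants. The Statistical analysis plan section allows adjustment for gender and baseline weight or BMI in sensitivity analyses, as an option.

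**The concern.** In a cluster trial, randomising ranches makes the ranches comparable. It makes the enrolled workers comparable only if enrolment does not depend on the allocation. Here workers select themselves within each ranch after the ranch has been allocated. If a crew knows or can infer its arm, a worker on an intervention ranch is deciding about a weight and diabetes program, and a worker on a control ranch about communication training. The arms could then differ at entry in motivation to lose weight, in baseline weight or in gender mix.

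The gender mix could matter in itself. The pilot, as described in the Background, found small reductions that were statistically significant in women but not in men. A bias of this kind is systematic: it does not shrink with sample size, and adjusting for measured covariates does not remove the unmeasured part.

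**Working it through.** The article gives no figure for this point, so the check is first a reading of the sections together and then an illustration of size.

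**1. Is the allocation fixed before enrolment?** Yes. The Randomization section and Table 3 agree.

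**2. Could the allocation reach the people who recruit or volunteer?** The article leaves this open.
- Research assistants are stated to be unblinded, and they screen, obtain consent and take baseline.
- Participants are stated to be unblinded, without saying from when.
- Promotores make the first approach, and they also deliver the program ("The intervention will be conducted by" promotores). Their knowledge of allocation at the information visits is not stated.
- No section says that allocation is kept from crews or staff until baseline is complete.

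**3. Does an entry step mean something different by arm?** It can. Willingness to attend weekly sessions is one criterion, but the sessions differ by arm.

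**4. Does matching help?** No. Pairs are matched on location, berry type and, where feasible, size. The selection in question happens among workers within a ranch, after allocation.

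**5. Must allocation come first?** Nothing in the article requires it. Allocation uses ranch-level factors and availability only, and sessions already wait for baseline. The Data collection section has both arms measured concurrently.

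**6. How large could the bias be?** The SD of 5% and the target differences of 3% and 4% come from the Power calculation section. All other inputs are assumptions.

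*Illustration A.* Bias = (difference between arms in mean motivation, in SD) × (correlation of motivation with percent weight change) × (outcome SD).
- 0.2 × 0.3 × 5 = 0.30 percentage points; 0.30/3 = 10% of the 3% target.
- 0.3 × 0.3 × 5 = 0.45 percentage points; 0.45/3 = 15% of the 3% target.

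*Illustration B.* Bias = (difference between arms in the share of motivated volunteers) × (extra weight loss of motivated workers, whatever their arm).
- 0.10 × 1 = 0.1 percentage points; about 3% of the 3% target and 2.5% of the 4% target.
- 0.30 × 4 = 1.2 percentage points; 40% of the 3% target and 30% of the 4% target.

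**7. How does this compare with random error?** Take 300 workers per arm, SD 5% and the article's inflation formula 1 + (m − 1) × ICC at its stated m = 100.
- ICC 0.01: factor 1.99; standard error = √(2 × 25/300 × 1.99) = 0.58 percentage points.
- ICC 0.05: factor 5.95; standard error = √(2 × 25/300 × 5.95) = 1.00 percentage points.

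The bias in illustration A is thus between 0.30/1.00 = 0.3 and 0.45/0.58 = 0.8 of one standard error. (Table 2 prints larger inflation factors than the formula gives at m = 100. That is a separate matter; they would make these standard errors larger.)

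**The case against.** The best case for the plan has four parts.

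- **The article shows a risk and no observed imbalance.** This stands. A reader might infer that the two arms' volunteers are different populations, or that crews are told their arm at the information visits. The documents support neither. The blinding statement names participants and data-collecting research assistants, leaves promotores out, and is explained by the nature and place of the intervention. What workers were told may be set out in scripts that are not shown.
- **Controls are recruited by the same approach.** This is the nearest safeguard, but it describes a procedure. The same visits and calls can be made with the allocation known, so it does not establish concealment.
- **Early allocation has a practical use.** This stands in part. A reader might infer that it serves no purpose because sessions wait for baseline anyway. But starts are staggered by crew, and a deferred draw would hold ready crews until the matched ranch is finished. The workers are seasonal and need only plan to stay 3 months, while the program runs 6 to 12 weeks, so waiting could cost some attendance.
- **The plan already offers adjustment and process data.** Gender and baseline weight or BMI may be adjusted for, and sign-up, screening and enrolment are tracked. The adjustment is optional, confined to sensitivity analyses, and cannot reach unmeasured motivation. The tracking makes the reporting below cheap.

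It is also true that unblinded participants are unavoidable once sessions start. That does not prevent concealment up to the end of baseline.

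**Conclusion.** The point holds as a possible bias that the stated order of steps leaves open. Ranches are allocated first, the staff who enrol workers are unblinded, session content differs by arm, and no concealment until baseline is described. Neither the common recruitment approach nor the optional sensitivity adjustment removes the risk.

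Its size and direction are unknown. The 0.30 to 0.45 percentage points rest on an assumed motivation shift of 0.2 to 0.3 SD and an assumed correlation of 0.3. The second set of assumptions spans 0.1 to 1.2 points, which shows how far the figure depends on its inputs. Neither is an estimate of the bias in this trial, and the documents do not show that it favours either arm. On the first set it is modest against a 3% target, but it would not diminish with more workers.

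**What to change.** **For any pair not yet recruited:** hold the information sessions, screening, consent and baseline at both ranches with one identical script, and only then draw and reveal the pair's allocation. The sample size is unaffected. The cost is that crews ready early wait until the matched ranch finishes baseline, which may lose some attendance among seasonal workers.

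**For pairs already recruited:** the Study status section says follow-up data collection is ongoing, so this may be most or all of them. Report the numbers approached, interested, eligible and enrolled by arm, compare baseline characteristics by arm, and state possible recruitment bias as a limitation of the primary result. The Process evaluation section already tracks sign-up, screening outcomes and enrolment, so this costs little beyond tabulation. It can reveal measured imbalance; it cannot exclude unmeasured differences.

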### Setting and site selection

The study is being conducted in Oxnard, California. The recruitment and intervention will happen at RBI, a partner or affiliate company ranches (administratively supported by RAC). *Promotores* will give presentations about the study to individual work crews to invite them to participate. All subjects will be RBI, partner or affiliate company employees and study sessions will be held in the field on ranches. Some supplemental activities will be held in RAC offices or in the community (library, community center).

#### Intervention

UCD, in collaboration with RAC, developed a program by integrating aspects of several programs to create a culturally tailored curriculum appropriate for delivery in an agricultural setting. The program was designed to educate participants about obesity, diabetes and healthy lifestyles, motivate changes in their current diet habits, and provide a supportive participatory group setting. Core principles of *Salud para su Corazon*, developed by the U.S. National Heart, Blood and Lung Institute (NHLBI) are complemented with *5 Pasos*, being implemented in Mexico by the Mexican Government [24, 25]. These two programs are used synergistically to implement the goals of the intervention. Because of the simplicity of its message, *5 Pasos* provides the general framework for the program. The five steps are: 1) Move, 2) Drink water, 3) Eat fruits and vegetables, 4) Measure (food portions and weight), and 5) Share (information learned and healthy habits). The *Salud para su Corazon* curriculum is a user-friendly, bilingual program for *promotores* developed by NHLBI specifically for Latino communities. The *Salud* curriculum will be used to supplement some of the visual aids used during the delivery of the intervention program. The intervention will be implemented on farms where workers spend a considerable amount of time every day. The intervention will be delivered over 6–12 weeks and the length of follow-up will be 1 or 1.5 years depending on when the worker was enrolled in the study.

The core intervention program will consist of 12 lessons (Table 1). In order to maximize participation and retention in this group which averages long work hours, the core intervention sessions will take place at the ranch during a meal break during work hours. Sessions will be presented to work crews in a format analogous to tailgate trainings. Tailgate trainings are gatherings of small groups of workers around the tailgate of a truck, in the field, or other spot for a brief, informal and focused training session on a single topic.

**Table 1 Tab1:** PASOS Curriculum

Session	Topic
1	Introduction to PASOS and the five steps toward a healthy lifestyle
2	Understanding the importance of having a healthy heart
3	Body mass index
4	Understanding blood pressure and keeping it within healthy levels
5	Learning about diabetes
6	Understanding diabetes and side effects
7	Understanding cholesterol and keeping it within healthy levels
8	Children and overweight
9	Healthy portions
10	Choosing healthy meals 1
11	Choosing healthy meals 2
12	Review and Graduation

The intervention will be conducted by *promotores* who will receive extensive training on curriculum content; framework of the intervention; group management skills and implementation of the intervention. In addition, the *promotores,* will be taught effective presentation delivery skills to ensure that they understand the material and are able to motivate and support participants.

